## Abstract

Introduction: Weight regain after bariatric surgery remains a relevant and worrisome topic, requiring greater understanding and involvement in research into new adjuvant treatments. This study aims to compare the preliminary effectiveness and feasibility of the Mindfulness-Based Health Promotion and Attachment-Based Compassion Therapy programs as opposed to usual treatments (workshops) on the eating behavior of patients with progressive weight gain after bariatric surgery in Brazilian patients at a private clinic. It was hypothesized that both interventions are feasible and that the self-compassion program may be more effective than the mindfulness program. Methods: The study will be divided into two phases: a cross-analytical study of those who underwent bariatric surgery and a randomized controlled trial only with the ones who had weight regain. Interventions will be conducted for eight weeks synchronously with three assessment points (baseline, post intervention, and 6-month follow-up), both online. The primary outcome will be a change in eating behavior. Secondary outcomes will include improved quality of life, enhanced body image satisfaction and reduced distortion (Brazilian Silhouette Scales for adults), better weight management (maintenance or weight reduction), increased frequency of activity and monitoring with the surgery team. Qualitative data will also be collected by online identification of a sub-sample of participants. Results: Improvements are expected in eating behavior, weight, reverse progressive weight gain, classification of self-image, quality of life, and levels of mindfulness, self-compassion, and anxiety. Conclusion: This study seeks to gather preliminary evidence on the effectiveness of mindfulness and compassion training for the adjunctive treatment of progressive weight gain in post-bariatric patients.

*Clinical Trials.gov* Registration ID: NCT04171713.

Specifications table

**Table utbl0001:** 

Subject area:	Medicine and Dentistry
More specific subject area:	Mindfulness and eating behavior
Name of your protocol:	Mindfulness and compassion-based programs for patients undergoing bariatric surgery
Reagents/tools:	N.A.
Experimental design:	This is a mixed methods study (quantitative-qualitative) divided into two phases: a cross-sectional study (phase 1) to refine the hypotheses and a randomized controlled feasibility study (phase 2).
Trial registration:	Clinicaltrials.gov: NCT04171713
Ethics:	This study was approved by the Research Ethics Committee from the local Institutional Review Board, under the CAAE protocol reference number 18529519.5.0000.5505. Participants will sign the Informed Consent Form online and data confidentiality will be guaranteed.
Value of the Protocol:	• First randomized controlled feasibility study with people who underwent bariatric surgery and regained weight on mindfulness and self-compassion. • Intervention with two different approaches and three assessment points studding five facets of the eating behavior (baseline, post intervention, and 6-month follow-up). • Improvements are expected in eating behavior, reversing progressive weight gain, classification of self-image, quality of life, and in levels of mindfulness, self-compassion, and anxiety.

## Introduction

Obesity is a public health problem, especially in developing countries, where 85 % of worldwide premature deaths from noncommunicable diseases occur [1]. Brazil is following the global trend, with 20,3% obese men and 22,6% obese women, according to the latest national survey [2]. For those with Obesity class III, e.g. with the Body Mass Index (BMI) ≥ 40 Kg m^-1^², or those with the BMI between 30 and 35 kg m^-1^² (Obesity class II) in the presence of clinical comorbidities, bariatric surgery still offers better results than non-surgical treatments, which have short-term benefits in metabolic markers and comorbidity reduction [[3], [4], [5], [6], [7]]. Usually, during the first years after bariatric surgery, patients tend to be more compliant with the recommendations regarding diet and lifestyle. Then, their compliance naturally decreases with time, which is reflected by body weight gain and the resultant deterioration in quality of life [8,9] Sustainable weight loss in long-term follow-up remains, however, a complex and relevant topic in the bariatric field [5].

Weight regain greatly affects health, causing economic repercussions on the management of ongoing obesity and the return of comorbidities [4]. This weight loss-and-regain cycle can also be psychologically devastating [4], inducing feelings of disappointment, frustration, fear of returning to their heaviest weight, and shame [10]. Weight regain has mental suffering related aspects as well, including depression and anxiety [11]. Moreover, body image dissatisfaction has been related as a sensitive indicator of low psychological well-being after surgery [12]. This whole set of factors, and others, can lead to constant contact with negative emotions.

This issue has no simple solution [6]. The inability to permanently change behavioral responses to environmental conditions and pressures hinders successful treatments [7]. Several of overweight or obese individuals eat compulsively in response to negative emotions [13]. Among the bariatric population with weight regain, studies report other additional compulsion aspects related to eating, such as binge eating, night eating, grazing, and uncontrolled eating [8,11,14,15]. The increase in lack of control eating seems to increase weight regain and to decrease the perception of quality of life components [16].

Along with standard behavioral weight-loss strategies, topics such as acceptance, motivation, emotional-based eating, reward-based/impulsive eating, physical activity, and self-compassion may also be useful to the post bariatric surgery patient, improve physiological and psychological outcomes [15]. The third wave of behavioral psychotherapies could help post-bariatric patients improve since it is essential for the development of modern psychotherapy, characterized by new themes including metacognition, cognitive fusion, emotions, acceptance, mindfulness, self-compassion, dialectics, spirituality, and therapeutic relationship [17]. Among these, this study emphasizes the mindfulness-based and compassion-based programs, which have gathered increased interest over the last three decades [18], particularly from those who work on health promotion and self-compassion.

The main goal of Mindfulness-Based Programs (MBPs) is to develop autonomy, self-efficacy and empowerment of people through the capacity generated by training in mindfulness, aspects considered fundamental in the modern concept of health promotion [19]. On the other hand, compassion-based interventions (CBIs) seeks to affect empathic processes and prosocial emotions, including decreased self-criticism, decreased rumination, reception of negative life events, and regulation of emotions [19].

Although both MBPs and CBIs training programs contain meditative practices of attentional and constructive families, MBPs have a greater amount of attentional practices while CBIs have more of constructive practices, thus differing structurally in the specific cognitive mechanisms that impact on well-being.

‘Attentional’ refers to the systematic training of the intentional ability to initiate, direct and/or sustain attentional processes, strengthening the ability to be aware of the processes of thinking, feeling and perceiving, thus developing their cognitive mechanisms of attention regulation and meta-awareness. In contrast to mindfulness practices, which often focus on simply monitoring cognitive and affective patterns, ‘constructive’ meditations involve systematically altering the content of thoughts and emotions, strengthening psychological patterns that promote well-being, by developing coping mechanisms as perspective taking (process of considering how one or another would think or feel in a particular situation) and re-appraisal (process of changing how one thinks or feels about situations and events in such a way that one's response to them is altered) [20].

CBIs produced larger effects for eating behavior and rumination outcomes compared with control interventions [21]. Higher levels of self-compassion and practice of attention and acceptance strategies have improved individuals’ desire to ignore cravings for food [22], indicating that training can help monitor and inhibit eating, which then increases happiness and psychological resilience [23].

Mindfulness-Based Programs have achieved positive treatment effects. Evidence supports its use for obesity-related eating behaviors, including binge eating, emotional eating, and external eating, suggesting moderate to largely effective outcomes on weight loss [24]. On the bariatric population, there is only one pilot study that used an approach with elements of Mindfulness-Based Stress Reduction (MBSR), Mindfulness-Based Eating Awareness Training (MB-EAT), and Mindfulness Self Compassion (MSC) for ten weeks to test the feasibility, acceptability, and effectiveness of this approach compared to a standard intervention, concluding that the approach was highly achievable and acceptable to patients and also effectively decreased emotional intake, but not reverse weight gain [25]. Mindfulness training is not yet part of routine care for bariatric patients [15], neither is compassion training. Additional research is needed to determine whether these strategies are effective in the long term and whether they can be routinely introduced into the clinical practice [26]. No previous studies have directly compared specific CBIs with conventional MBIs effects on progressive weight regain.

The aims of the present study are twofold: to describe the protocol for both (1) the cross-sectional study to refine the hypotheses and (2) a Randomized Controlled Trial (RCT) to compare the preliminary effectiveness and feasibility of the Mindfulness-Based Health Promotion (MBHP) and Attachment-Based Compassion Therapy (ABCT) programs regarding the usual care on the eating behavior of patients with progressive weight gain after bariatric surgery. It was hypothesized that both interventions are feasible and effective to improve eating behavior, but the compassion-based program is superior to the mindfulness-based program because it addresses specific psychological skills (such as self-compassion) that mediate the effects on eating behavior and well-being.

## Methods

### Study design

This is a mixed methods study (quantitative-qualitative) divided into two phases: a cross-sectional study (phase 1) to refine the hypotheses and an RTC (phase 2). The report of this study will be following the STROBE Statement for Cross-Sectional Studies and the Consolidated Standards of Reporting Trials (CONSORT). The study's headquarters will be a private clinic specialized in obesity treatments located in Uberlândia, Minas Gerais State, Brazil, founded in 2011. About 8000 bariactric surgerys have been conducted on the clinic.

### Phase 1: cross-sectional study

#### Study design

This is a cross-sectional study to be conducted with patients who underwent bariatric surgery until 2020, seeking to identify the main differences between patients with weight maintenance, with expected weight gain and progressive weight regain, and thus refine the hypotheses of the study's Phase 2.

#### Participants

Participants will be included in the sample: adults aged ≥18 who underwent sleeve gastrectomy or Roux-en-Y Gastric Bypass, after at least two years. The sample considers patients with ‘weight maintenance’, those who keep the minimum weight achieved after bariatric surgery (nadir); patients with ‘expected weight gain’, a recovery <20 % of weight lost in the long term, according to the Brazilian Society of Bariatric and Metabolic Surgery (SBCBM) [27] and patients with ‘progressive weight regain’ those who recovery > 20 % of in the long term.

#### Measurements

All data will be collected by patient report using an electronic online form (SurveyMonkey®) containing closed and open questions distributed among a socio-demographic survey and validated scales in Portuguese.-Sociodemographic and others: An instrument containing, age, gender, marital status, associated diseases, lifestyle habits, and weight evolution before and after surgery and other questions related to objectives, such as questions about adherence to post-surgical follow-up consultations, nutritional recommendations and attendance to support groups, psychological and/or psychiatric treatment and physical activity.-The 21-item Three-Factor Eating Questionnaire (TFEQ-R21): This scale has 21 items that assess three aspects of eating behavior: cognitive restriction, emotional eating, and uncontrolled eating. Higher scores indicate greater cognitive restraint, uncontrolled eating or emotional eating [28,29].-Repetitive Eating Questionnaire [Rep(eat)-Q]: This is a 12-item questionnaire to assess grazing, with two graze subtypes: repetitive eating and compulsive grazing. An overall average of the 12 items will be calculated. The scores for each domain will be calculated as an average of all items in each domain. Higher scores indicate more presence of grazing feeding behavior [30].-Binge Eating Scale (BES): This is a scale of 16 items and 62 statements that was built in three stages: characteristics of binge eating, severity of each characteristic, and an external criterion of severity (frequency, amount of food, and degree of emotion involved in an episode). Each statement corresponds to a number of points from 0 to 3, ranging from absence “0″ to maximum severity “3″ of binge eating. The overall score will be categorized as follows: non-binging ≤ 17 points, moderate binging 18 to 26 points, and severe binging ≥ 27 points. [31,32].--Moorehead-Ardelt Quality of Life Questionnaire II (M-A QoLQII): This is a self-administered questionnaire which addresses quality of life, updated from a part of the Bariatric Analysis and Reporting Outcome System. It contains six questions with a 10-point Likert scale that assesses the following domains: general self-esteem, physical activity, social contacts, job satisfaction, pleasure related to sexuality, and focus on eating behavior. The scores for each item and the overall average of the 6 items will be used to generate an overall quality of life score. Higher scores indicate better self-perception of quality of life. [33].-Brazilian Silhouette Scales for Adults (BSSA): This scale has 15 images for each gender, with a white figure centered on a black background. The adult scales include the BMI averages corresponding to each figure ranging from 12.5 to 47.5 kg m^-12^, with a constant difference of 2.5 points [34]. This scale will be used to assess body image distortion, when the participant indicates which image, they resemble the most (considered distorted body image when they choose a silhouette different from their current BMI) and to assess body image dissatisfaction when the participant responds what image would they like their bodies to be. Dissatisfaction with body image will be analyzed based on the disagreement between the current silhouette and what they would like to look like, and the participants will be classified as satisfied and dissatisfied. Then, subjects with body dissatisfaction will be dichotomized into those who wanted to increase their body size (dissatisfaction due to thinness) and those who wanted to reduce their body size (dissatisfaction due to excess weight).-Mindful Attention Awareness Scale (MAAS): The MAAS is an instrument that assesses mindfulness and consciousness levels according to time. This 15-item scale indicates how often the participants experienced each of the situations described in the items. Higher scores reflect higher levels of dispositional attention [35,36].-Self-Compassion Scale – Short Form (SCS-SF): The brief 12-item SCS-SF assesses the feeling of compassion for the self in dimensions of self-kindness, self-judgment, common humanity, isolation, mindfulness, and over-identification. Higher scores mean more self-compassion. [37,38].-Hospital Anxiety and Depression Scale (HADS): This 14-item scale measure signs of anxiety and depression. It has three stages for the two subscales: possible anxiety and depression disorders (8–10 points), probable anxiety and depression disorder (11–14 points), and severe disorder (15–21 points) [39,40].-Experiences in Close Relationship Scale – Reduced (ECR-R-Brazil): This 10-item scale measures adult attachment in the context of love relationships, containing two dimensions of attachment, anxiety and avoidance. Higher scores indicate higher levels of attachment-related anxiety and avoidance [41,42].

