#### Outcomes

The primary outcome will be a change in the eating behavior (TFEQ-21, Rep (eat)-Q, and BES) at all steps. Secondary outcomes will be improved quality of life (M-A QoLQII), increased satisfaction with body image and reduced distortion (BSSA), better weight management (maintenance or weight reduction), increased frequency of physical activity, and monitoring with the surgery team. The explicative variables will be the level of mindfulness (MAAS), self-compassion (SCS-SF), anxiety (HADS), and attachment style (ECR-R).

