#### Assessment

Quantitative and qualitative assessments will be performed before the intervention (T0), immediately after the intervention (T1) and at the six months follow-up (T2). Participants will respond to the same electronic form used in Phase 1 of the study at the three evaluation moments (T0, T1 and T2) and after the intervention they will be able to respond subjectively about their adherence to the sessions, frequency of performing formal practices and report if there were unexpected effects (adverse events) in periods T1 and T2 by completing another electronic form [46]. After six months of follow-up, the control group will be offered the intervention (MBHP or ABCT) considered most effective to improve eating behavior (Fig. 2).

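### Body-image outcomes are scored as any-mismatch and yes/no classes that discard the size of the discrepancy, and the analysis plan does not say whether classes or scores will be compared

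*Protocol article*

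**What the plan says.** The scoring is in the Protocol article, Phase 1, Measurements. Of the BSSA it says "This scale has 15 images for each gender", with figure BMIs running from 12.5 to 47.5 "with a constant difference of 2.5 points". Two classifications follow.

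- **Distortion:** "considered distorted body image when they choose a silhouette different from their current BMI". No tolerance is given, nor any rule for assigning a BMI to a figure.
- **Satisfaction:** "Dissatisfaction with body image will be analyzed based on the disagreement between the current silhouette and what they would like to look like", after which "the participants will be classified as satisfied and dissatisfied". The dissatisfied are then divided by direction: "subjects with body dissatisfaction will be dichotomized into those who wanted to increase their body size" and those who wanted to reduce it.

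The rule carries into the trial. Phase 2, Assessment, states "Participants will respond to the same electronic form used in Phase 1 of the study" at T0, T1 and T2. Phase 2, Outcomes, lists "increased satisfaction with body image and reduced distortion (BSSA") among the secondary outcomes.

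Phase 2, Analyses plan, compares the scales by t-test or Mann-Whitney test, compares the change (Δ) in the study variables, and correlates the silhouette scales with the other instruments. It does not say in what form the BSSA enters any of these.

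**The concern.** The outcomes are worded as matters of degree (more satisfaction, less distortion), but the scoring rule records only presence or absence. A participant who moves from five figures too large to one figure too large is dissatisfied both times. The split by direction does not help, because it carries sign and not size.

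For distortion, a coarse scale is compared with a continuous quantity and every mismatch counts. A one-figure difference that ordinary perception error could produce is put in the same class as a gross misjudgement. Noise of that kind can fill the distorted class and dilute any real improvement.

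If the trial compares these classes between arms, a moderate benefit on two named secondary outcomes could easily be missed, although the answers collected would have shown it.

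**Working it through.** **Figures in the protocol.**
- Scale: (47.5 − 12.5)/2.5 + 1 = 15 figures, which agrees with the text.
- Sample size: reading 30% against 5% as proportions improving, two-sided 5%, 80% power, the two-proportion formula with continuity correction gives 43 per group (36 without). The stated 43 is reproduced. It was sized on the primary outcome and is used below only as the evaluable number per arm.

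**Inputs not in the protocol (assumed).** BMI with mean 32 and SD 5; perception error SD 1 to 3 BMI units without bias; a treatment shift of 0.6 SD in the current-minus-desired gap; 5%, 10% or 20% of controls satisfied.

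**1. Satisfaction: score against yes/no at 43 per arm.**

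Score: expected test statistic = 0.6 × √(43/2) = 2.78. Power ≈ Φ(2.78 − 1.96) = Φ(0.82) ≈ 79%; the exact t-test also gives 79%.

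Yes/no: the same shift moves the satisfied proportion from p to q = Φ(Φ⁻¹(p) + 0.6). Power = Φ[(q − p − 1.96·se₀)/se₁], with se₀ pooled and se₁ unpooled. For p = 10%, q = 24.8%, se₀ = 0.0818, se₁ = 0.0802, so power = Φ[(0.148 − 0.160)/0.0802] ≈ 44%.

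| Controls satisfied | Treated satisfied | Power, yes/no | Power, score |
|---|---|---|---|
| 5% | 14.8% | 33% | 79% |
| 10% | 24.8% | 44% | 79% |
| 20% | 40.5% | 54% | 79% |

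**2. Second check, with the gap in whole figures.** The gap is simulated as a rounded normal variable, with satisfied meaning a gap of exactly zero. The true improvement is one figure.

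| Mean gap (SD), figures | Dissatisfied, control → treated | Power, yes/no | Power, score |
|---|---|---|---|
| 4 (2) | 97.2% → 93.5% | 0.13 | 0.63 |
| 3 (2) | 93.3% → 87.9% | 0.14 | 0.63 |
| 2 (1.5) | 88.8% → 78.9% | 0.24 | 0.86 |

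**3. How large a shift the binary version can detect.** At 43 per arm, 80% power needs a fall of about 25 percentage points from a control rate of 90%, or about 22 points from 95%.

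**4. Distortion with nearest-figure matching.** Actual and perceived BMI are each assigned to the nearest figure, and any difference counts as distorted.

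| Perception error SD (BMI units), no bias | Classed as distorted |
|---|---|
| 1 | 32% |
| 2 | 56% |
| 3 | 68% |

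None of these simulated participants has a systematic misperception, so the whole distorted class is random error. Over a wider range of assumptions (error SD 0.5 to 5, bias 0 or 2.5 BMI units) the proportion runs from 16% to 92%. Allowing one figure either way, it runs from 0% to 51%. The result therefore depends heavily on a tolerance that the protocol does not set.

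**The case against.** The strongest reply is that the protocol does not confine the trial analysis to classes. The classification sits under Phase 1, which is cross-sectional. The Phase 2 Analyses plan uses t-tests, Mann-Whitney tests, Δ and correlations, methods that suit ordered or numeric silhouette data, and the raw choices are retained. This stands in part: a numeric analysis may be intended. But the plan never says so, and the Phase 1 scoring is the only BSSA scoring in the document and belongs to the form reused in Phase 2. The two sections need reconciling whichever was meant.

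A second reply is that how BMI is matched to a figure is a detail an article may leave to the instrument's source or a fuller protocol. That is fair as regards the matching itself. It does not remove the stated choice to count every mismatch and to classify satisfaction as yes/no.

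A reader might infer that almost everyone will be classed as distorted. On a literal reading that follows: with BMI to one decimal, only 1 value in 25 falls on a figure (2.5/0.1 = 25), so 96% of perfectly accurate raters would mismatch. But the figures carry average BMIs and participants pick the one they most resemble, so nearest-figure matching is the more natural reading, and it gives a split sample.

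It is also fair that the body-image inputs are assumed, that 43 per arm was not sized for this outcome, and that a preliminary study promises no particular power on secondary outcomes. The comparison of score with class at the same sample size does not depend on such a promise.

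**Conclusion.** The point holds in a limited form. The stated scoring discards the size of the discrepancy, and the Analyses plan leaves open whether that scoring governs the trial comparison. If it does, a moderate change in satisfaction is poorly detected: power of 33% to 54% against about 79% in the first set of assumptions, and 0.13 to 0.24 against 0.63 to 0.86 in the second. Any-mismatch coding of distortion lets random perception error alone fill about a third to two thirds of the sample.

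It would go too far to conclude that the outcomes cannot detect change. The binary version keeps some power, and falls of about 22 to 25 points from control rates of 95% and 90% reach 80%. Nor do the documents establish that nearly all participants start dissatisfied. That is plausible in people who have regained weight, but no expected proportion is given. All the power and misclassification figures rest on assumed distributions. The primary outcome is unaffected.

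**What to change.** For Phase 2, state that the BSSA is analysed numerically:

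- **Distortion:** BMI of the chosen figure minus current BMI, both signed (direction of misjudgement) and absolute (its size). Rounding to the grid then costs at most half a step, 2.5/2 = 1.25 BMI units.
- **Dissatisfaction:** current figure minus desired figure.
- **Comparison:** between arms at T1 and T2, adjusted for the T0 value.
- **Classes:** keep satisfied/dissatisfied and thinness/excess weight as descriptive summaries. If a distorted/not distorted class is also reported, state how BMI is matched to a figure and what tolerance applies.

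Amend Measurements and Analyses plan so that both describe the same BSSA variables. The cost is a few sentences: the questionnaire, the assessments and the sample size stay as they are, and the same answers are used.
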